#### **4.8 Maintenance of the trial treatment randomization codes and procedures for breaking codes**

The need for continuous safety monitoring (NO and NO2 levels in inhaled gas, methemoglobin levels) requires the presence of an unblinded team. This team will consist of the trial manager and locum nurses to assist with night coverage. The randomization code will be kept in a locked cabinet accessible by the trial manager only. The code will be consulted at the point of randomization, at which point the iNO or room

air placebo will be started by the trial manager. The code will be used for the purpose of tabulating data for the DSMB review on a quarterly basis, and at the midpoint of patient enrolment. Data will be disaggregated by treatment arm, although the treatment received (iNO or placebo) will not be known to the DSMB (“Group A” and “Group B”).

Unblinding of individual patients may be required under exceptional circumstances if there are safety concerns. The Jinja pediatrician may request this information from the trial manager in the rare event that knowledge of study gas may influence patient care. The entire trial population will be unblinded after completion of enrolment. Statistical analysis will be conducted in a blinded fashion, with patients assigned to “Group A” of “Group B” by the trial manager.

We will assess whether blinding has been successful by asking key trial persons (caregivers, health professionals, outcome assessors) to guess patients’ treatments and compare the answers with the actual treatments[88]. Statistical differences from chance alone will be evidence that trial blinding was compromised.

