#### ***Blinding***

We will assess whether blinding has been successful by asking key trial persons (caregivers, health professionals, outcome assessors) to guess patients' treatments and compare the answers with the actual treatments[88]. These will be recorded on the CRF.

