## **9.2 Number of subjects planned to be enrolled**

We will enrol 180 patients (approximately 90 in each treatment arm).

Based on a recent clinical trial of L-arginine as adjunctive treatment for severe malaria, among patients who subsequently recovered, Ang-2 decreased by 2700pg/mL/day (95%CI 1800-3600pg/mL/day)[33]. We assume that a 50% change in this parameter would represent a clinically significant therapeutic effect. By standard calculations for normally distributed data, 80 patients per group will provide 80% power to detect a difference between two treatment arms of 1350pg/mL/day at  $p=0.05$  (two-sided). This corresponds to a 50% difference in the rate of change of Ang-2 between the arms. To account for possible dropout, loss to follow-up, and/or non-evaluable data of 10% of patients, approximately 90 patients per study arm are required.

However, these calculations do not reflect the analytic plan. Therefore, a simulation study was performed. A number of assumptions needed to be made, such as within patient correlation and Ang-2 variability. Patient Ang-2 data were simulated using a

multivariate normal distribution. A simple autoregressive correlation structure was used with correlations of 0.75, 0.5 and 0.25 for lags 1, 2 and 3 respectively. In previous studies, variability appears proportional to the mean[33]. Simulations were run with three different relationships where the standard deviation was taken to be 40%, 50% and 80% of the Ang-2 mean at each time point. Both groups were assumed to start at Ang-2 levels of 15,000 pg/mL and the average values at each of days 1, 2 and 3 based on the hypothesized slopes of Ang-2. One thousand replications were performed at each standard deviation relationship and treatment effect. The mixed effects models were fit and the likelihood ratio test was used to test the hypothesis of no time by treatment interaction at the 5% level (two tailed). Table 4 shows the results of the power simulations.

Table 4: Power simulations for 90 patients per group

| Standard Deviation
(% of mean) | Slope Difference               |                                        |                                        |
|-------------------------------------------|---------------------------------------|----------------------------------------|----------------------------------------|

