### **9.3 Level of significance to be used**

The threshold for statistical significance will be  $\alpha=0.05$ .

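### The blinding check counts any above- or below-chance guessing as a compromised blind, so a clinically visible iNO effect can flag a blind that is intact

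*Protocol*

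**What the plan says.** Protocol section 4.8 plans to test the blind by "asking key trial persons (caregivers, health professionals, outcome assessors) to guess" the allocation and setting the answers against the true one. It then states how the result will be read: "Statistical differences from chance alone will be evidence that trial blinding was compromised". Section 4.9, under Quality – Blinding, repeats the procedure and adds only "These will be recorded on the CRF". Neither place says when the guess is made, asks what it rests on, or treats a guess based on the child's progress differently from one based on a leak.

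Other sections bear on the reading:
- Section 3 hypothesises a benefit on clinically relevant outcomes as well as on Ang-2.
- Section 4.9 has trial nurses note each shift whether the child can sit unaided. Section 9.1 has the blinded treating clinicians document sitting, coma resolution and discharge.
- Section 6.1 allows the mask to come off early as the child improves.
- Sections 4.3(b) and 4.7 describe two teams and gases that cannot be told apart. These protect concealment; they do not change how guesses are interpreted.

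**The concern.** A guess can be right for two reasons: the rater learned the allocation, or the rater inferred it from how the child did. The stated rule credits every departure from chance to the first. In this trial the raters observe recovery directly, and early mask removal is a second cue tied to recovery. If iNO speeds recovery visibly, raters who guess iNO for the quick recoverers will beat chance with the blind intact.

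At stake is a pre-stated inference that can be wrong when the treatment works. Time to sit unsupported and time to discharge are documented by treating clinicians, so a finding that the blind was compromised would weaken their credibility. Reinterpreting the flag once results are known would look like special pleading, and section 9.6 labels departures from the planned analyses as post hoc.

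**Working it through.** The protocol gives no figure for this check, so there is nothing to reproduce. The calculation below asks how often the rule would flag an intact blind.

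**Inputs from the protocol**
- Sample size, section 9.2: "We will enrol 180 patients (approximately 90 in each treatment arm". One guess per child gives n = 180.
- Significance level, section 9.3: 0.05.

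**Assumptions (not in the protocol)**
- The test is an exact two-sided binomial test of correct guesses against 50%. The protocol names no test.
- Concealment is perfect and guesses are independent.
- Recovery times are exponential, with hazard ratio h for iNO against placebo.
- A rater guesses iNO if the child recovers before the pooled median time, and placebo otherwise. In a second version half of the guesses are coin flips.
- h = 1.3, 1.5 and 2.0 show a range.

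**Step 1: size with no visible effect.** With n = 180 the test rejects at 104 or more, or 76 or fewer, correct guesses. At a true rate of 50% this happens 4.4% of the time.

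**Step 2: share of correct guesses.** With the placebo hazard set to 1, the pooled median t solves (e^−t + e^−ht)/2 = 0.5. The correct share is c = [(1 − e^−ht) + e^−t]/2. For h = 1.5, t = 0.562, e^−t = 0.570 and e^−ht = 0.430, so c = (0.570 + 0.570)/2 = 0.570. With half of the guesses random, the share is 0.5 + (c − 0.5)/2, here 0.535.

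**Step 3: probability of a flag.**

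| Recovery hazard ratio | Correct, all guess from recovery | Flagged | Correct, half random | Flagged |
|---|---|---|---|---|
| 1.0 | 50.0% | 4.4% | 50.0% | 4.4% |
| 1.3 | 54.5% | 21% | 52.3% | 8% |
| 1.5 | 57.0% | 45% | 53.5% | 14% |
| 2.0 | 61.8% | 88% | 55.9% | 33% |

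**Step 4: cross-check without survival times.** Suppose raters guess iNO exactly when recovery looks fast, with 90 children per arm. The correct share is [p(iNO) + 1 − p(placebo)]/2, where p is the proportion with fast recovery.
- 50% on placebo against 60% on iNO: 55% correct, flagged 25% of the time.
- 50% against 70%: 60% correct, flagged 75%. A comparison of guesses between arms gives 79%.
- 50% against 70% with half of the guesses random: 55% correct, flagged 25%.

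Both models show the same thing: the flag rate climbs with the visible effect although nothing has leaked.

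**The case against.** Five objections deserve weight.

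**Consequence.** The rule calls a difference evidence and attaches no action. The primary endpoint is a laboratory measure and the analysis is run on masked groups A and B. A reader might infer that any effective treatment would make the trial discredit its own blind. The documents do not support that: an effect on Ang-2 alone need not be visible to the raters, and for modest visible effects the flag is far from certain. This stands and limits the point to interpretation.

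**Rater model.** The upper figures need every rater to follow recovery against a pooled median that no rater knows, and the hazard ratios are assumed. This also stands, which is why the half-random figures are shown beside them.

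**Absent detail.** Timing, a don't-know option and reasons for guesses are often left to an SAP, SOP or CRF. That would answer a complaint about missing detail. It does not answer this one, because the protocol itself states the inference.

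**Leakage in one arm.** A reader might also infer that the check misses leakage confined to the iNO arm, for example through methemoglobin events, and so errs in both directions. The documents do not support this, since no pooled test is specified. Nor would testing by arm cure it. If 10% of iNO children were disclosed, accuracy would be 0.10 + 0.90 × 0.5 = 55% in that arm and 52.5% overall; exact tests detect this about 15% and 9% of the time. Weak detection of small leaks reflects the sample size, not this sentence.

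**The remedy.** Tying the guess to the end of study gas would place it at visible recovery for the fastest recoverers, because gas may stop when the child improves. That is right, and the change proposed here uses a fixed hour instead.

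**Conclusion.** The point holds in a limited form. The rule in section 4.8 can flag an intact blind if iNO has a clinically visible effect and raters guess from it, with a probability that rises with that effect: about 8–21%, 14–45% and 33–88% at recovery hazard ratios of 1.3, 1.5 and 2.0, against about 4–5% with no visible effect. These figures rest on one guess per child, an exact test and an assumed rater model; they illustrate the mechanism and do not forecast this trial. What is affected is the reading of the blind and, through it, of the clinician-assessed secondary endpoints. The primary Ang-2 test is untouched. The wording should be changed, but the flaw does not threaten the trial's main conclusion.

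**What to change.** Reword the rule in section 4.8, and section 4.9 (Quality – Blinding) to match:
- Collect the guess once, at a set hour after study gas starts, early enough that response is unlikely to be apparent. Do not trigger it by gas stopping.
- Offer a don't-know option and record the main reason: gas or equipment, methemoglobin, being told, clinical course, or none.
- State that the unblinded team is not among the raters; the term health professionals does not exclude its locum nurses.
- Report guesses by arm and by rater type.
- State that above-chance guessing attributed to clinical course cannot be separated from efficacy and is not by itself evidence of a compromised blind, whereas above-chance guessing for other reasons is.

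The cost is a few reworded sentences and some CRF tick boxes, since the guess is already collected. Treatment and the primary analysis do not change. There are two drawbacks: an early guess misses later leakage, and reasons are self-reported, so a leak could be put down to clinical course.

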#### **4.9 Data to be included on the case report forms (CRF)**

##### ***Study participants***

After initial stabilization, participants recruited to the trial will have a screening form completed, according to inclusion and exclusion criteria. Patient age, co-morbidities, nutrition status (weight and height), malaria rapid diagnostic test result, anemia, methemoglobin level, and willingness to participate in the trial will be documented on the screening form and will be the basis of deciding on whether a child is eligible for the study. Eligible, consenting participants will then undergo a full history and physical

examination, the results of which will be recorded on the CRF. Study entry blood work will include the following, and a checklist on the CRF will be completed to ensure that the appropriate specimens have been collected for laboratory testing:

- CBC and differential
- Electrolytes
- Creatinine
- Lactate
- Venous blood gases
- Blood culture
- CSF gram stain and culture (as appropriate)
- CSF cell count and differential (as appropriate)
- HIV point-of-care test
- Serum and plasma sample for Ang-2

***Primary endpoint: Daily rate of change of Ang-2***

Four venous blood samples, appropriately collected, aliquoted, and stored are required for this endpoint. The CRF will document the successful collection of venous samples on a daily basis over the course of the study, and any problems that may compromise the sample quality. In the case of missing/incomplete data, the CRF will document the reason for missing data.

***Secondary endpoints:***

***48 hour and 14-day mortality***

The CRF will document whether the patient was alive or deceased or lost to follow-up at 48 hours after admission, and at the 14-day follow-up visit.

***Time to fever resolution***

Trial nurses will document vital signs on the CRF (every 4 hours for the first day, every 8 hours thereafter). The time to achieve a temperature  $<38^{\circ}\text{C}$  for  $\geq 24$  hours will be derived from these data.

***Time to sit unsupported***

Trial nurses will document at the end of each shift whether the patient is able to sit unsupported and the time to achieve this endpoint will be derived from these data.

***Time to hospital discharge***

CRF completed by the medical officers will include the admission and discharge dates.

***Time to parasite clearance***

Parasite density will be followed longitudinally over the course of the hospital admission. The CRF will document that a peripheral sample has been obtained for parasitemia.

***Incidence of recrudescence at day 14***

The 14-day follow-up visit will document that a peripheral blood sample has been obtained for determination of parasite density.

***Whole blood lactate level***

A handheld lactate meter will be used by medical officers to document whole blood lactate levels at each blood draw. The CRF will record the lactate levels, the time of collection, and any difficulties that may compromise the validity of the data.

***Neurocognitive outcome at 6 months after discharge***

CRFs for the neurocognitive outcome will document findings of testing.

**Safety****Adverse events**

Adverse events will be recorded on the patient CRF as well as a log tabulating the cumulative adverse events. The adverse events will be described by the nature of the adverse event, date of onset, date of resolution, possible or probable causal association with study gas, severity, and expectedness.

**Adverse drug reactions**

A checklist of adverse drug reactions (based on product monograph) will be completed on a daily basis by medical officers. This will require a daily review of patient notes during the admission, including vital signs. Age specific norms will be used to classify vital signs as normal or abnormal. The following adverse drug reactions that occurred in at least 5% of patients receiving INOmax in the CINRGI study with event rates >5% and greater than placebo event rates[89]:

- Hypotension
- Withdrawal
- Atelectasis
- Hematuria
- Hyperglycemia
- Sepsis
- Infection
- Stridor
- Cellulitis
- Other (specify)

In the event that the study gas is discontinued or withdrawn (section 5.3 Subject withdrawal criteria), the date, time and reason will be documented on the CRF as well as a dedicated form (checklist) for study gas discontinuation/withdrawal. This form will also document the resolution of the abnormality (vital signs, methemoglobin, oxygen

level) and any sequelae or complications. If the patient is re-challenged with study gas, the timing will be recorded. Criteria for temporary discontinuation are as follows:

- Methemoglobinemia
- Elevated inspired NO2 concentration
- Persistent hypoxemia
- Evolving respiratory distress
- Unexplained tachycardia
- Unexplained hypotension
- Any study drug related adverse event that, in the opinion of the investigator, makes it unsafe for the subject to continue

Criteria for permanent discontinuation of study gas are as follows:

- Refractory methemoglobinemia
- Hemoptysis
- Acute kidney injury
- Other adverse event that, in the opinion of the investigator, makes it unsafe for the subject to continue.
- Adverse event that repeats upon re-challenge
- Subject or guardian's discretion
- Investigator's discretion

Monitoring for these adverse drug reactions will require laboratory investigations including glucose and creatinine, measured on at least a daily basis. The CRF will include laboratory data (point-of-care test results).

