## PROTOCOL SUMMARY

**Title:** **Inhaled Nitric Oxide as Adjunctive Therapy for Malaria: a Randomized Controlled Trial**

**Background:** Severe malaria remains a major cause of global morbidity and mortality. While the use of artemisinin-based antimalarial therapy has improved outcomes in severe malaria, the mortality rate remains high. Adjunctive therapies that target the underlying pathophysiology of severe malaria may further reduce morbidity and mortality. Endothelial activation plays a central role in the pathogenesis of severe malaria, of which the angiogenic factors angiopoietin-1 (Ang-1) and angiopoietin-2 (Ang-2) have recently been shown to function as key regulators. Nitric oxide (NO) is a major inhibitor of Ang-2 release from endothelium and has been shown to decrease endothelial inflammation and reduce the adhesion of parasitized erythrocytes. Low-flow inhaled nitric oxide gas (iNO) is a US FDA-approved treatment for hypoxic respiratory failure in neonates. Based on compelling data on the efficacy of iNO in experimental cerebral malaria in animal models, coupled with the documented safety of iNO in clinical practice and trials for other diseases, we propose a randomized clinical trial of iNO for the adjunctive treatment of severe malaria in Ugandan children.

**Population:** 180 children 1-10 years old admitted to hospital with moderately severe and severe malaria; 90 treated with iNO (80ppm) and 90 with placebo (room air).

**Site:** Jinja Hospital Children's Unit (Jinja, Uganda).

**Study Duration:** 12-18 months (recruitment and acute outcomes); 6 additional months to complete neurocognitive testing of cohort.

**Study Participant Duration:** 3 days; follow-up neurocognitive testing after 6 months.

**Objective:** To determine the efficacy of inhaled nitric oxide for the adjunctive treatment of *P. falciparum* malaria.

Our *specific aim* is:

**To determine whether supplemental low flow inhaled nitric oxide gas (80 ppm) in addition to Ugandan Standard of Care treatment reduces levels of**

**angiopoietin-2 (Ang-2) from baseline in children with moderately severe and severe malaria compared to Standard of Care treatment alone.**

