| Davidson. Pediatrics. 1998 [71]                      | prospective multicentre controlled RCT                     | 155 (iNO n=114, nitrogen gas n=41)          |                               | Term infants with PPHN                                                  | evaluate clinical efficacy of iNO in neonates with respiratory failure                                                                                  | iNO improved oxygenation, no differences in mortality or ECMO                                       | inhaled, 5, 20 and 80 ppm                                          | Elevated methemoglobin (>7%) in 13/37=35% patients receiving 80ppm; and nitrogen dioxide (NO 2 >3%) in 7/37=19% patients receiving 80ppm |
| Dobyns et al. J Pediatr. 1999.[72]                   | prospective, multicentre, placebo-controlled RCT           | 108 (placebo gas n=55, iNO n=53)            |                               | children, median age 2.5y                                               | determine whether iNO could attenuate progression of lung disease in AHRF, and whether early initiation of low-dose iNO results in improved oxygenation |                                                                                                     | inhaled at 10pp from 3-7 days after entry                          | methHb none, NO 2 high none, no difference in ICU-dependent therapies                                                                    |
| Michael JR et al. Am J Resp Crit Care Med. 1998.[73] | prospective, multicentre RCT                               | 40 (no treatment n=20, increasing iNO n=20) | adults and children age 1-79y | between 12h and 25d after ARDS developed                                | whether iNO therapy improved oxygenation vs. no treatment within 72hr of randomization, as measured by persistent decreases in FIO 2         |                                                                                                     | inhaled at 5, 10, 15, 20 ppm x6h each for 72h                      | bleeding (1/20 required blood tx, 1/20 ICH after thrombolytic - both iNO groups); no MethHb                                                         |

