#### **(b) Blinding**

In previous clinical trials using iNO[69], one of the design and implementation challenges was establishing the blinding procedures while titrating and monitoring concentrations of iNO, as well as anticipated dose-related increases of methemoglobin and NO2 concentrations. A trial manager not involved in patient care will be responsible for the monitoring and recording of iNO, NO2, and methemoglobin levels. Thus, the establishment of two teams, one blinded team making all clinical assessments and therapeutic decisions, and another unblinded team monitoring the delivery of the treatment gas and assessing the development of potential toxicities, will allow the drug

to be delivered safely while minimizing the possibility that direct knowledge of treatment allocation would influence the care delivered to the patient.

iNO cylinders will be attached to ventilation system in all patients. The unblinded study site investigator will administer and monitor the delivery of NO or placebo (room air), according to the treatment arm to which the patient has been randomized.

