#### **4.7 Accountability procedures, including placebo and comparators**

iNO will be compared head-to-head with room air placebo in a randomized, parallel group design. All patients will receive standard-of-care antimalarial agents and supportive therapy for their severe malaria. Treatment and placebo will be indistinguishable for participants, caregivers and health professionals. All patients will wear a mask and receive room air, with supplemental oxygen as needed, delivered via compressor. The treatment group will also receive iNO mixed with the air flow. The dilution will be such that there will not be a perceptible difference between treatment and placebo flow rates.

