## **6 TREATMENT OF SUBJECTS**

### **6.1 Description of intervention**

*Product:* Gaseous nitric oxide

*Dose:* 80 ppm

*Dosing schedule:* Continuous

*Route:* Inhalation (non-rebreather HiOx® face mask)

*Treatment period:* Maximum 72 hours (may be discontinued earlier if patient recovers and no longer tolerates face mask)

Gaseous NO (delivered with air and oxygen as carrier) at a concentration of 80 parts per million (ppm) will be administered continuously by inhalation (non-rebreather HiOx®

face mask) for a maximum of 72 hours. Subjects in the control arm will receive room air as a placebo for a maximum of 3 days. The iNO dose of 80 parts per million is US-FDA approved for use in neonates (see *INOMax product monograph*).

To monitor the inspired nitric oxide, nitrogen dioxide (NO2) and oxygen concentrations, a US-FDA approved gas monitor will be used. Should the NO or NO2 concentrations fall outside the targeted range, an operator set alarm will sound. The trial manager or designee (unblinded) will be available on a 24 hour basis to respond to monitor alarms.

Nitric oxide will be delivered as long as possible with the above device, up to a maximum of 72 hours. However, as the subject improves in the course of the disease, recovers consciousness, begins ambulating, and/or no longer tolerates the mask delivery system, the study gas may be discontinued earlier than 72 hours. At this point after significant disease resolution, it is expected that the continued benefit of iNO will be negligible. The trial manager or designee (unblinded) will be responsible for initiating the study gas (iNO or room air placebo), monitoring the inhaled NO, NO2 and O2 levels as well as patient methemoglobin levels, responding to any monitor alarms, initiating corrective actions, and informing the treating physicians, if necessary. We will monitor peripheral oxyhemoglobin saturation, and use the minimum inspired O2 concentration (above 21%) required to maintain a PaO2 ≥ 92%.

As a primary safety measure, every patient will be monitored with a US-FDA approved pulse CO-oximeter for methemoglobin and arterial oxygen saturation. This will assure, metabolically, that too much nitric oxide is not being inhaled and that the inspired oxygen concentration is correct.

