For the purposes of safety monitoring and reporting, adverse drug reactions will include temporary as well as permanent discontinuation of the study gas. Criteria have been established for temporary and permanent study gas discontinuation, and are listed in sections 4.6 Description of stopping rules/discontinuation criteria, and 5.3 Subject withdrawal criteria (terminating trial treatment).

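### Section 4.9 puts the reason for stopping study gas, including methemoglobinemia and raised inspired NO2, on the patient CRF, which may reveal allocation to staff meant to be blinded, almost only in the iNO arm

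*Protocol*

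**What the plan says.** **The promise.** Section 4.3(b) sets up "one blinded team making all clinical assessments and therapeutic decisions", and gives the monitoring and recording of NO, NO2 and methemoglobin to a trial manager outside patient care. Section 4.7 states: "Treatment and placebo will be indistinguishable for participants, caregivers and health professionals". Section 4.8 limits the unblinded team to the trial manager and locum night nurses, and expects individual unblinding, at the paediatrician's request, to be rare. Section 9.1 relies on blinded treating clinicians to document sitting unsupported, coma resolution and discharge.

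**The recording rule.** Under Adverse drug reactions, section 4.9 requires that after a stop "the date, time and reason will be documented on the CRF as well as a dedicated form (checklist) for study gas discontinuation/withdrawal". The reasons listed there include methemoglobinemia, raised inspired NO2 and refractory methemoglobinemia, and the form also records how an abnormal methemoglobin resolved. The same section says: "A checklist of adverse drug reactions (based on product monograph) will be completed on a daily basis by medical officers". Section 8.1 adds that "adverse drug reactions will include temporary as well as permanent discontinuation of the study gas".

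**The bedside.** In section 6.1 an alarm sounds when NO or NO2 leaves its target range, and a nurse is there throughout gas treatment. The unblinded manager's duties include "initiating corrective actions, and informing the treating physicians, if necessary".

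**The concern.** Most reasons for stopping gas (hypoxemia, respiratory distress, tachycardia, hypotension, mask intolerance) can arise in either arm and reveal nothing. Two cannot be treated that way. Placebo is room air, so raised inspired NO2 is not expected there. Children with baseline methemoglobin above 2% are excluded (section 5.2), so methemoglobinemia that appears during treatment points strongly to iNO. A CRF entry naming either reason tells its reader the likely arm, and the disclosure runs almost entirely one way.

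The staff who handle the CRF also document sitting unsupported and discharge, choose co-treatment (unrestricted under section 6.2) and judge whether events are related to study gas. Knowledge of allocation can shift each of these. The children revealed are also not a random subset of the iNO arm: they are those with a toxicity finding.

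**Working it through.** **Step 1. Who sees the reason?** Reading the sections together:

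- Section 4.9 sends the reason to the CRF in addition to the dedicated form, and names nobody for the entry.
- Section 8.1 makes every gas discontinuation an adverse drug reaction. Section 4.9 has medical officers complete the daily reaction checklist from the patient notes. Section 8.2 has medical officers and/or nurses monitor these reactions, which are recorded on CRFs.
- In section 4.9 (Intervention), trial nurses record time on gas on the CRF each shift.
- In section 13, medical officers complete the study forms, nurses complete observation charts, and both go into one folder per participant.
- In sections 5.3(d) and 8.4, the medical officer follows a child withdrawn for an adverse event until the abnormal parameter resolves or stabilizes. For methemoglobinemia, that parameter is methemoglobin.
- No section restricts the reason to the unblinded team, or says that alarms are masked or mimicked on placebo.

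The likely readers are therefore the staff whom sections 4.3(b) and 9.1 call blinded.

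**Step 2. How many children?** The protocol states no rate of gas stops for these reasons and no rate of lost blinding. Only Table 2 (section 2.2) gives related figures. Its own percentages reproduce: 13/37 = 35.1% (printed 35%) and 7/37 = 18.9% (printed 19%). Below, each proportion x/n has an exact (Clopper-Pearson) 95% interval and is multiplied by the 90 planned iNO children.

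| Table 2 source | x/n | Rate (95% CI) | Of 90 |
|---|---|---|---|
| Children, median age 2.5 y, 10 ppm: no methemoglobinemia reported | 0/53 | 0% (0 to 6.7%) | 0 (up to 6.1) |
| Neonates, 20-80 ppm: dose reduced for methemoglobin 5-10% | 11/114 | 9.6% (4.9 to 16.6%) | 8.7 |
| Neonates, 80 ppm: raised NO2 | 7/37 | 18.9% (8.0 to 35.2%) | 17.0 |
| Neonates, 80 ppm: methemoglobin >7% | 13/37 | 35.1% (20.2 to 52.5%) | 31.6 |

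The denominator 114 is that trial's whole iNO arm. The paediatric row also reports no high NO2.

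If methemoglobin and NO2 both reveal the arm, the share with either lies between the larger rate and the sum: 13/37 = 35.1% to (13 + 7)/37 = 54.1%, or 31.6 to 48.6 of 90 children.

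**Step 3. Would the planned guess test catch it?** Assume one guess for each of 90 iNO children, a share u revealed and guessed correctly, and the rest guessed at random. Correct guesses = u + (1 - u)/2.

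- u = 0.0965: 0.0965 + 0.4518 = 54.8% correct. Power of a two-sided exact test against 50% is about 14%.
- u = 0.35: 0.35 + 0.325 = 67.5% correct. Power is about 92%.

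The test in section 4.8 would probably miss leakage near 10%, and it can only report the problem afterwards.

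**The case against.** The strongest reply is that the protocol never says that blinded staff write down the reason. Section 4.9 is in the passive. The monograph-based checklist names neither methemoglobinemia nor NO2, though it has an open line for other events. Section 4.3(b) gives the recording of methemoglobin and NO2 to the trial manager, so the stop form may already belong to the unblinded team, and operational detail sits in an SOP that is not shown. This stands as far as authorship goes: medical-officer entry is an inference. It does not remove the conflict, because the reason goes on the CRF as well as the form, whoever writes it, and nothing keeps it from the other CRF users.

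Two stronger readings are tempting, and the documents support neither.

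- *That the blind is lost for 10 to 35% of iNO children.* Those ends are 11/114 and 13/37. They are neonatal methemoglobin findings at other cut-offs, the first also at mixed doses, and measure neither gas stops nor unblinding. The paediatric row with 0/53 must be set beside them, although at 10 ppm it does not settle the matter either.
- *That section 6.1 bypasses the unblinding procedure of section 4.8.* Informing physicians is conditional, and the content of the message is not given.

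It is also fair to say that section 4.3(b) acknowledges the difficulty and aims only to minimize the influence of knowing the arm. The primary endpoint is a laboratory measure, laboratory personnel have no access to the linked database when testing (section 11), and the analysis is run on coded groups (section 4.8). Finally, treating physicians may need a methemoglobin result, so a remedy that hides it from them would intrude on clinical management.

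**Conclusion.** The point holds as an inconsistency between the recording rule and the blinding promise. Followed as written, section 4.9 can reveal allocation for some iNO children and hardly any placebo children, contrary to sections 4.3(b), 4.7 and 9.1. The audible alarm in section 6.1 adds a second route. This rests on two inferences: that medical officers or trial nurses see the CRF entry, and that methemoglobinemia or raised NO2 during treatment signals iNO. For methemoglobinemia that is strong suggestion rather than proof, since the baseline exclusion itself allows for raised levels without iNO.

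The size is unknown. Any figure from near 0 to about 54% is an assumption that carries rates from other ages, doses, delivery and cut-offs into this trial. The exposed outcomes are time to sit unsupported, time to discharge, co-treatment and causality judgements. Ang-2 and mortality are largely protected, so the primary conclusion is not in question. The change is worth making because it is cheap and prevents a one-sided leak that the guess test may not detect.

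**What to change.** 1. In section 4.9, let the clinical CRF record only that study gas went off or on, with date and time.
2. Have the unblinded team complete and hold the reason and the methemoglobin, NO and NO2 values on the dedicated form that already exists, apart from the patient folder until database lock.
3. Reconcile the alarm and the informing of treating physicians in section 6.1 with sections 4.3(b) and 4.8. Any arm-revealing disclosure made for care or safety stays available and is logged as an unblinding event.
4. In section 4.7, replace the claim that the arms cannot be told apart with a description of the blinding actually achieved.

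None of this should limit safety information that treating physicians need. Clinical stopping criteria and management stay as they are.

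Cost: rewording of the CRF, the protocol sections above and the related SOP. The unblinded team and the form are already in place. The downside is that the stop reason sits in a separate file that has to be merged after lock.
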